## Abstract

**Background:**

Patients undergoing maintenance hemodialysis (MHD) endure weakness due to prolonged dialysis treatment, such as the continuous decline of muscle strength in patients, which will have varying degrees of impact on human physiological, psychological, and social functions. Effective nonpharmacological interventions can improve their mental health and quality of life (QoL).

**Objective:**

This study aimed to investigate the effects of sitting Baduanjin combined with acupoint massage on improving the frailty status of patients undergoing MHD and evaluate whether it can significantly improve their physical activity, alleviate depressive emotions, and comprehensively improve their QoL.

**Methods:**

This is a randomized controlled study to be conducted in the Affiliated Hospital of Chengdu University of Traditional Chinese Medicine, comprising 114 patients to be treated using MHD. Patients who meet the inclusion and exclusion criteria will be randomly divided into 3 groups: the control group will receive only conventional hemodialysis and care, the acupoint massage group will receive acupoint massage treatment in addition to the control group treatment, and the sitting combined with acupoint massage group will receive sitting Baduanjin combined with acupoint massage and the control group treatment. We aim to comprehensively evaluate the clinical efficacy by comparing the FRAIL (Fatigue, Resistance, Ambulation, Illness, and Weight Loss) scale scores, grip strength, 10 times sit-to-stand test, Self-Rating Depression Scale scores, and QoL (Short Form Health Survey Questionnaire) scores before and after 8 weeks of treatment among the 3 groups. Statistical analysis will be conducted using the Statistical Package for the Social Sciences software (version 25.0; IBM Corporation).

**Results:**

The first participant was enrolled on August 8, 2024. As of August 2025, a total of 52 participants have been fully registered, and the intervention is currently in progress. We expect the completion of this trial to occur within the year 2025.

**Conclusions:**

The results of this study can provide a scientific basis for the future treatment of patients with asthenia in hemodialysis.

## Introduction

### Background

Maintenance hemodialysis (MHD) is the primary treatment for end-stage renal disease. It effectively removes metabolic toxins from the body, prolongs patient survival, and improves quality of life (QoL) [1]. Frailty is a nonspecific state resulting from decreased physiological reserves or multisystem dysfunction, leading to increased vulnerability and reduced stress resistance. This makes individuals more susceptible to adverse clinical events, even in response to minor external stimuli [2]. It is a prevalent and debilitating clinical syndrome that significantly affects the QoL of patients undergoing MHD treatment [3]. Frailty is primarily characterized by unintentional weight loss, diminished grip strength, slowed walking speed, reduced physical activity, and self-reported exhaustion [4]. The presence of 1 or 2 of these criteria indicates a prefrail state, while the presence of 3 or more criteria can confirm frailty. A recent survey conducted in the United States revealed a 9% prevalence of frailty among the older population, with an even higher prevalence of 44% among those classified as prefrail [5]. A Chinese study revealed that 5.6% of individuals aged ≥60 years were classified as frail, while 49.3% exhibited characteristics indicative of prefrailty [6]. A review of international studies revealed that the prevalence of prefrailty among patients undergoing hemodialysis ranged from 50% to 63%, while the prevalence of frailty itself fluctuated between 33% and 47% [7-10]. A Chinese study revealed a prevalence of 60.7% for prefrailty and 44.8% for frailty in patients undergoing hemodialysis [11,12].

These findings indicate that all age groups of adults undergoing hemodialysis exhibited a significantly elevated prevalence of frailty, exceeding that observed in the general older population. This highlights the need for increased attention to this issue [7]. As the duration of dialysis increased, the patients exhibited a progressive decline in muscle strength, a reduction in activity levels, and the development of frailty. This condition can influence a range of physiological, psychological, and social functions, as well as self-care abilities. In addition, it increases the risk of falls, rehospitalization, and mortality, thereby reducing the QoL [13,14]. Frailty was identified as an independent predictor of all-cause mortality in patients undergoing MHD for more than 5 years [15].

Previous studies link frailty in patients undergoing MHD to physical function, depressive symptoms, and QoL [16]. Prolonged dialysis causes substantial amino acid and protein loss; patients with chronic renal failure with low protein intake (insufficient for bodily needs) have reduced muscle synthesis and impaired physical function [17]. In addition, calcium-phosphorus imbalance in patients undergoing MHD reduces skeletal muscle and joint function, while prolonged sitting and lying impairs muscle strength or mass and physical activity [16]. Due to irreversible progression and long treatment, patients often have anxiety and depression. A systematic review notes a bidirectional depression-frailty relationship: patients with depression face higher frailty risk, and patients with frailty are more likely to have depressive symptoms [17]. Declines in physical function and depression fuel frailty, creating a vicious cycle that lowers QoL, raises rehospitalization and death risks [18]. However, frailty is dynamic and reversible; timely detection or management can delay or reverse it, improving prognosis [19]. Sarcopenia is the core pathological basis of frailty in patients undergoing MHD, with most having low grip strength and activity levels [20]. MHD has a strong adverse association with frailty, with evidence from multiple studies. First, frailty is highly prevalent in patients undergoing MHD: a meta-analysis of 16 studies (2446 patients) reported a pooled frailty prevalence of 41% [21]. Second, frailty significantly elevates adverse outcomes in patients undergoing MHD. A systematic review including 23 studies (10,333 patients) showed patients with frailty undergoing MHD had higher all-cause mortality and all-cause hospitalization [22]. Third, specific factors mediate this association: xerostomia and poor nutrition correlate with frailty, jointly explaining 45.6% of frailty variance in older patients undergoing MHD [23]; age, hypoalbuminemia, depression, and malnutrition are independent frailty predictors in patients undergoing MHD [24]. This underscores frailty as a key clinical concern requiring attention in the management of patients undergoing MHD management. The prevalence of prefrailty is notably high among patients undergoing MHD. Prefrailty, an early and reversible condition between nonfrailty and frailty, can lead to adverse outcomes such as increased unplanned hospital admissions and a higher risk of other chronic diseases [24].

Early identification and treatment of frailty in patients with myocardial hypertrophy are critical for the management of this condition. Baduanjin, a low-to-moderate-intensity aerobic exercise, is based on traditional Chinese medicine (TCM) theories and integrates the yin-yang and meridian theories. Baduanjin comprises standing and sitting forms, distinguished by their gentle and slow movements. These are characterized by simplicity, ease of learning, safety, efficacy, and the absence of venue and time restrictions [25]. The practice of sitting Baduanjin has many beneficial effects, including regulation of the body, breath, and mind, as well as harmonization of the 5 viscera [26]. Furthermore, it mitigates the risk of falls and other mishaps resulting from muscle atrophy and diminished endurance, rendering it a suitable choice for patients with frailty undergoing MHD. Modern research has demonstrated that Baduanjin exhibits beneficial regulatory effects on multiple systems of the body, not only resisting aging but also significantly improving limb muscle strength, alleviating anxiety and depression, improving fatigue states, relieving pain, enhancing cardiopulmonary function, and, with long-term practice, strengthening the body and improving disease resistance [27-29].

Baduanjin can significantly improve sleep quality, alleviate anxiety and depression, and improve fatigue in patients undergoing MHD [29]. Another study indicated that 5-element music combined with Baduanjin helps reduce fatigue and alleviates frailty in patients undergoing MHD, improving the QoL [30]. From the perspective of TCM, frailty in MHD is mainly caused by a deficiency in organ functions, qi, blood, yin, and yang, with prolonged deficiency leading to fatigue. The core pathology involves spleen and kidney deficiencies. Sitting Baduanjin can harmonize qi and blood, balance yin and yang, and coordinate organ functions to achieve a balanced state, thereby improving physiological functions.

Furthermore, TCM emphasizes the overall regulatory role of the meridian system. Studies have demonstrated that acupoint massage can improve limb function, negative emotions, sleep quality, and fatigue [31,32]. Studies using acupoint massage on patients undergoing hemodialysis revealed significant improvements in fatigue and QoL with specific acupoints, including Zusanli (ST36), Sanyinjiao (SP6), Taixi (KI3), Yongquan (KI1), and Neiguan (PC6) being particularly effective [33].

### Current Research Gap

Although studies have explored the effects of Baduanjin and acupoint massage on patients undergoing MHD, there are still knowledge gaps. Most studies focus on improving specific indicators, but there is a lack of assessment of the patients’ frailty status. Baduanjin improves muscle function of patients undergoing hemodialysis, reduces systemic inflammation, and enhances skeletal muscle–related indices [34]. Massage relieves lower limb cramps [34] and boosts sleep quality via hot stone therapy [35]. Yet, massage only targets single symptoms (no effects on muscle mass and inflammation); Baduanjin needs nutritional support, covers a few frailty symptoms, and has limited skeletal muscle benefits [34,36]. Their combination could comprehensively address frailty, synergistically protect muscles, and improve frailty via multiple mechanisms. Regarding the effectiveness of combining sitting Baduanjin exercise and acupoint therapy in improving the frailty of patients undergoing MHD, there is also a lack of high-quality evidence.

### Unique Contributions of This Study

This study aims to address these research gaps through a randomized controlled trial that systematically evaluated the effects of combining sitting aduanjin with acupoint massage on frailty in patients undergoing MHD treatment. This study makes several contributions to the field. First, it is the first to combine the sitting form of the 8-section brocade with acupoint massage to provide an 8-week comprehensive nonpharmacological intervention strategy with long-term follow-up. A systematic approach is used in this study to evaluate numerous indicators in patients undergoing MHD, including frailty, grip strength, lower limb function, depression status, and QoL. The findings contribute to the evidence base for effective and high-quality nonpharmacological interventions for patients with frailty undergoing MHD.

### Purpose and Significance

This study aims to investigate the effects of various interventions on frailty. The primary objective is to investigate whether combining sitting Baduanjin with acupoint massage could improve frailty in individuals with mild-to-moderate heart disease, reduce muscle atrophy, inhibit physical function decline, and alleviate depressive symptoms. This approach is hypothesized to significantly improve patients’ social life and QoL.

The following section outlines the foundation for further research on acupoint massage for MHD-induced frailty. This research will investigate clinically applicable TCM nondrug treatment strategies, providing new ideas for preventing and treating MHD-induced frailty using TCM. The intervention is low-cost and easily accessible. This combined intervention strategy is cost-effective, not venue- or equipment-specific, and has significant clinical implications.

### Expected Outcomes

It is anticipated that the frailty status of patients undergoing MHD will improve significantly, with substantial enhancement of muscle strength and lower limb function. Depressive symptoms will be alleviated, and mental health and QoL will be enhanced. Furthermore, this study will serve as a reference for effective and convenient intervention measures to further improve frailty in patients undergoing MHD.

## Methods

### Research Design

A randomized controlled trial design is used to evaluate the impact of integrating Baduanjin exercise with acupoint massage on the prevalence of frailty in patients undergoing MHD treatment.

### Participants

A total of 114 patients undergoing MHD who met the inclusion and exclusion criteria were selected from the Hemodialysis Center of the Affiliated Hospital of Chengdu University of TCM (Textbox 1).

Textbox 1.Inclusion, exclusion, removal, withdrawal, and termination criteria for patients undergoing maintenance hemodialysis.
**Inclusion criteria**
Age: 45‐75 years with end-stage renal disease (uremia stage).Dialysis duration: receiving hemodialysis treatment ≥3 months, 3 times a week, and 4 hours per session, with stable vital signs.Frailty status: evaluated using the FRAIL (Fatigue, Resistance, Ambulation, Illness, and Weight Loss) scale, with scores of ≥1 indicating prefrailty or frailty.Cognitive and communication ability: clear consciousness, normal hearing, and ability to communicate normally.Physical function: no physical activity disorders, no regular exercise, able to understand and follow demonstration actions.Acupoint skin condition: intact skin at acupoint massage sites.Voluntary participation: willing to participate in the study.

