### Sample Size Calculation

The sample size calculation formula for the multigroup mean is as follows:

$$n=\varphi^{2}\left(\sum_{i}s_{i}^{2}/g\right)/\left[\sum ({\bar{X}}_{l}-\bar{X}{)}^{2}/(g-1)\right]$$

where n represents the requisite sample size for each group, g represents the number of groups, and Si is the mean (SD) for each group. The values of φ are obtained from tables α, β, ν1, and ν2, with α=.05, β=.1, ν1=2, ν2=∞, and *φ*=2.52. A 2-sided test was used in this study, which stipulates that the test level α=.05, the test efficiency 1-β=.90, and the probability of a type II error is 0.10. The FRAIL scale score was used to calculate the effect size, and the average number of patients in each group, as previously described [37], was as follows: 3.29, 2.67, and 2.58, with SD values of 0.96, 0.87, and 1.02, respectively. These data were entered into the formula to calculate n=34. Considering the shedding rate of 10%, the actual required sample size for the 3 groups was estimated to be 38 per group, totaling 114 patients.

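### The planned FRAIL effect and SDs are not matched to the FRAIL ≥1 population being enrolled, so the unqualified 90% power is not supported

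*Protocol article*

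**What the plan says.** Textbox 1 (Inclusion criteria) admits patients on the FRAIL scale "with scores of ≥1 indicating prefrailty or frailty". The section on the primary evaluation indicator gives a range of 0 to 5, with bands at 0, 1–2 and ≥3. The Background explains why prefrailty deserves treatment, so admitting scores 1–2 is deliberate.

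Sample Size Calculation takes its effect from one cited study. The group figures are "3.29, 2.67, and 2.58, with SD values of 0.96, 0.87, and 1.02, respectively". It sets "the test level α=.05, the test efficiency 1-β=.90", uses "ν1=2, ν2=∞, and *φ*=2.52", and arrives at 34 per group, raised to 38 per group (114 in total) for 10% dropout. It does not say which groups the three means belong to, whether they are baseline or post-treatment values, or how that study selected its patients.

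On the case mix in hemodialysis, the Background reports that "the prevalence of prefrailty among patients undergoing hemodialysis ranged from 50% to 63%, while the prevalence of frailty itself fluctuated between 33% and 47" percent. On the population the results will serve, Unique Contributions of This Study speaks of "nonpharmacological interventions for patients with frailty undergoing MHD", whereas the Objective and the Conclusions speak of frailty among MHD patients in general.

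Statistical Inference compares the arms on post-intervention scores by one-way ANOVA or a rank-sum test, with no baseline adjustment described.

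**The concern.** The effect size and SDs carry the power claim, and they are useful only if they describe patients like those enrolled. The highest planning mean, 3.29, lies above the cut-off of 3. A cohort entered at FRAIL ≥1 and composed as the Background suggests would average well below that. It would also be more spread out, because it mixes scores of 1–2 with scores of 3–5. A wider spread lowers power even if the planned differences are reached. If benefit depends on how many points a patient has to lose, the differences shrink as well.

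A null result could then be read as evidence against the therapy when the trial had much less than the stated power. A positive result, worded for patients with frailty, would describe a narrower population than the one studied.

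**Working it through.** **1. The plan's own figure.** The inputs are the three means and SDs and φ = 2.52 from Sample Size Calculation.
- Average of the means: (3.29 + 2.67 + 2.58)/3 = 2.85. Sum of squared deviations: 0.2989. Divided by g − 1 = 2: 0.1494.
- Mean variance: (0.96² + 0.87² + 1.02²)/3 = 0.9063, so the SD is about 0.95.
- n = 2.52² × 0.9063/0.1494 = 38.5, so 39 per group. The printed 34 is not reproduced. That arithmetic slip is a separate matter, but it bears on the power below.
- Power from the noncentral F distribution, with λ = n × 0.2989/0.9063 and 2 and 3(n − 1) degrees of freedom: 84.8% at n = 34 and 88.8% at n = 38.

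**2. Expected mix among eligible patients.** Prefrail share = prefrail/(prefrail + frail), from the Background's international ranges: 50/97 = 51.5% to 63/96 = 65.6%. The Chinese figures (60.7% and 44.8%) sum to 105.5%, so they cannot describe one cohort and are not used here.

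**3. Could such a mix average 3.29?** At 51.5% prefrail, the mean score needed among frail patients is:
- (3.29 − 0.515 × 1.5)/0.485 = 5.19 if prefrail patients average 1.5, which is off the 0–5 scale;
- (3.29 − 0.515 × 2)/0.485 = 4.66 if every prefrail patient scores 2.

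At 65.6% prefrail the required value exceeds 5 in both cases.

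**4. Mean and SD of a mixed cohort.** Assumptions, not in the documents: prefrail mean 1.4–1.6 with variance 0.25, and frail mean 3.3–3.7 with variance 0.45. With prefrail share p and subgroup means a and b:
- mean = p·a + (1 − p)·b
- variance = p × 0.25 + (1 − p) × 0.45 + p(1 − p)(b − a)²

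At a = 1.5 and b = 3.5:

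| Prefrail share | Mean | Variance | SD |
|---|---|---|---|
| 51.5% | 2.47 | 1.35 | 1.16 |
| 65.6% | 2.19 | 1.22 | 1.11 |

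Over the full assumed ranges the mean is about 2.1–2.6 and the SD about 1.0–1.3.

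**5. Power of the three-group test at 34–38 per arm.** Three cases were run:
- *Absolute*: the planned differences 0.62 and 0.71 hold, with the mixed-cohort SD in all arms.
- *Proportional, same SD*: means scaled by 2.67/3.29 (a 19% fall) and 2.58/3.29 (a 22% fall), with the mixed-cohort SD in all arms.
- *Proportional, scaled SD*: as above, with the treated arms' SDs scaled by the same ratios.

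| Case | 51.5% prefrail, a = 1.5, b = 3.5 | 65.6% prefrail, a = 1.5, b = 3.5 | Full assumed range |
|---|---|---|---|
| Absolute | 68–73% | 72–77% | 58–87% |
| Proportional, same SD | 43–47% | 38–42% | 31–55% |
| Proportional, scaled SD | 54–59% | 48–53% | 40–68% |

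In the proportional cases at a = 1.5 and b = 3.5, the differences from control are 0.47 and 0.53 at 51.5% prefrail, and 0.41 and 0.47 at 65.6%.

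**The case against.** The strongest reply is that the mismatch is inferred, not shown. The enrolled FRAIL mix is not reported. The Background does not say that its prevalences were measured with FRAIL, and at one end of the range 48% of eligible patients would be frail. The cited study's entry rule is not visible. If its absolute effect and its SDs both carried over, power would be the 85–89% of the printed inputs. All of this stands, and it is why the figures here are ranges.

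A reader might infer several stronger points that the documents do not support:
- *The planning cohort averaged 3.29.* That is one group's mean, and the three average 2.85. Taking 3.29 as the untreated level is reasonable but is an inference.
- *The trial is mostly prefrail, so any conclusion rests on a frail minority.* This is a projection. Prefrail patients are included on purpose, and most statements of aim cover MHD patients generally.
- *The floor at 0 rules out the planned effect.* It does not: mean falls of 0.62–0.71 are smaller than the 1–2 points a prefrail patient can lose. Shrinkage needs the added assumption of proportional benefit.
- *Chance imbalance in the frail share is a further threat.* That variation is already in the mixed-cohort SD and the ANOVA error term, and it does not inflate the type I error.

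What remains after these concessions is that the article does not justify carrying the effect and SDs over to a FRAIL ≥1 population.

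**Conclusion.** The point holds as an unjustified planning assumption. The printed means do not fit a FRAIL ≥1 cohort with the article's own prevalences, and none of the cases examined reaches the stated 90% power: 85–89% on the printed inputs, about 58–87% with the planned absolute differences and a mixed-cohort SD, and about 31–68% if benefit is proportional. The lower ranges rest on the Background prevalences applying to this center, on the assumed subgroup means and variances, and on the cohort's baseline spread standing in for the post-treatment spread. They do not show that the trial is underpowered to any particular degree, and the lowest values are one pessimistic branch. The wording problem is narrower: it concerns only the phrase that limits the evidence to patients with frailty.

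**What to change.** 1. In Sample Size Calculation, withdraw the unqualified 90% power. Restate power or the detectable difference for the FRAIL ≥1 population, using the pooled baseline FRAIL mean and SD of the patients already enrolled (52 at submission), computed without reference to arm. Say whether the cited means are baseline or post-treatment values and how that study selected its patients.
2. Do not replace the claim with a statement that 90% power holds for a cohort averaging about 3.3. On the printed inputs it does not.
3. Word the conclusion for prefrail or frail patients, matching Textbox 1.
4. Optional: stratify the remaining allocation by FRAIL 1–2 versus ≥3. Changing allocation partway through is debatable. Stratification alone also leaves the baseline spread in an unadjusted post-score comparison, and any within-stratum claim would rest on small groups.

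The cost is one arm-blind tabulation of data already required at baseline, a few lines of text, and a less favorable stated power. This point asks for no extra patients or visits.

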**Exclusion criteria**
Neurological disorders: presence of neurological diseases or other uncontrolled chronic diseases.Severe complications: severe arrhythmias, angina, severe infections, malignancies, and renal osteodystrophy.Noncooperation: refusal to cooperate or psychiatric abnormalities preventing collaboration.Concurrent clinical trials: simultaneous participation in another clinical trial.
